## **10. Details of Benefit-Risk-Relation**

### **a. What are the expected benefits of the study?**

#### **aa) For participants?**

The interprofessional rehabilitation program includes evidence-based interventions to manage chronic non-specific low back pain, and it considers well-defined quality criteria for patient education programs in Germany. Furthermore it is characterized by a stronger patient orientation and therefore it is supposed to improve the individual success of treatment.

Chronic non-specific low back pain is a leading cause of disability worldwide. It affects all areas of life, e.g. social and work participation. Several theories and models, as well as results of randomised controlled trials emphasize the interplay between biological, psychological and social factors in the development of chronic pain (e.g. fear-avoidance model). Beyond simple additive effects, this refers especially to the relevance of mutually reinforcing between these factors. It is assumed, that the implementation of an interprofessional rehabilitation program improves self-management competencies to a greater extent compared to the standard multidisciplinary orthopaedic rehabilitation. This covers, for example, reduced fear-avoidance-beliefs, reduced further pain related cognitions (e.g. catastrophizing), adaptive pain coping strategies, improved self-efficacy, and the promotion of a physically active lifestyle to reduce symptoms of physical deconditioning.

Consequently, expected long-term results among the majority of participants of the intervention group are: improved self-reported functional ability, reduced pain intensity, and improved quality of life.

ab) for medicine?

- Introduction as interprofessional rehabilitation program for the German pension insurance
- Development of trainer manuals for the implementation of the interprofessional rehabilitation program in the routine of inpatient rehabilitation (e.g. contents, media, patient information, organisational assistance)
- Development and implementation of a training program for the rehabilitation team (Train-the-Trainer), transferring of the concept into curricula of relevant German organisations (e.g. DGOOC, DVGS, ZVK)
- Optimisation of quality and quantity in the inpatient orthopedic rehabilitation of chronic non-specific low back pain by current scientific standards

ac) for science (e.g. results, which do not immediately serve therapeutic purposes)

- Improved evidence on short-and long-term effects of interprofessional rehabilitation programs in chronic non-specific low back pain
- Exploration of underlying mechanisms of action
- Publications in national and international scientific journals

**b. What are the risks for persons who take part in the study?**

- ba) What kind of risks? What is the nature of the risks? Risk estimation, foreseeable risks attached to the treatment or any other study-related processes that might be used (including pain, inconvenience, problems, violations of personal integrity and measures to avoid and/or treat unpredictable/unwanted incidents)
- Evidence-based interventions will be carried out. The main focus is on the introduction of an interprofessional approach, as well as on a didactic modification with an interactive education format. There are no risks expected for the study participants.

bb) How probable is it that the risks are realized? How secure can the probability be estimated?

Not applicable.

**c. In your opinion, why is the potential risk defensible in relation to the expected benefit?**

Not applicable.

d. Is there an evaluation of interim findings to recognize a trend?

☐ Yes ☒ No

e. Have been criteria defined that would lead to a change or termination of the study.

☐ Yes, which? ☒ No

11. In case of clinical testings according to MPG (**not applicable**)

12. a) Is cooperation with a statistician intended?? ☐ Yes ☒ No

b) What statistical methods will be used?

The data analysis follows the usual standards in the evaluation of quasi-experimental control group design. To assess the long term treatment effect of interprofessional rehabilitation against multidisciplinary orthopedic rehabilitation, t-test or analysis of covariance (ANCOVA) respectively of functional ability measured with the FFbH-R at the 12-month follow-up will be used, adjusted for baseline differences, as primary analysis. Further possible baseline differences between both study groups in secondary variables (e.g. socio-demographic, medical) will be also addresses via regression analyses or analysis of covariance (Vickers, 2005). The data analyses will be supported by the methodology consulting of the Department of Medical Psychology, Medical Sociology, and Rehabilitation Sciences Würzburg.

13. a) Is this a multi-centre study (i.e. a study carried out by one single study plan but in different study centres and therefore carried out by different examiners)?

☒ Yes ☐ No

b) Have there been/Are there other places that carry out studies with the same or similar design?/ ☒ Yes, where? ☐ No

Effectiveness studies concerning medical rehabilitation or patient education programs implemented in medical rehabilitation about chronic low back pain (i.a. Bandemer-Greulich et al., 2008; Bosse et al., 2007; Greitemann et al., 2006; Mehnert et al., 2007; Schwarz et al., 2007; Metaanalyse: Hüppe & Raspe, 2003, 2005).

14. Who initiated the study?

[name]. [name] (University Erlangen), Dr. phil. [name] (University Würzburg) and Dr. med. [name] (German Society for Orthopedics and Orthopedic Surgery DGOOC, Asklepios Rehabilitation centre Schaufling)

15. Who funds the study? (*Please indicate if you applied for funding at a third, non-public party. If yes, which amount?*)

This project is funded in the module two of the first funding phase by the German Pension Insurance (Deutsche Rentenversicherung Bund) within the Research funding for care-oriented research “Chronic diseases and patient orientation” (<http://www.forschung-patientenorientierung.de/index.php/projects/first-funding-phase/module-two-phase-1/pastor-[name].html>) provided by German Federal Ministry of Research (BMBF), German Pension Insurance, Statutory health insurance, and Association of Private Health Insurance e.V. (funds: 311,484.00€).

16. The expense allowance for the assessment (<http://www.ethik.med.uni-erlangen.de/kosten.htm>) is performed by (please name contact):

[name]. [name]; Office: Frau [name], [contact]

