## II. Research project

1. Planned start for the study: 01/01/2008 (information gathering: 01/07/08) // expected end: 31/12/2010

Length of participation in the study for every single person: 12 months, 3 weeks

2. **Abstract of the project** (*maximum of 1.5 pages*):

**Objective.** The objectives of the present project are the development of a specific interprofessional rehabilitation program to promote active self-management of chronic non-specific low back pain, as well as to compare its effectiveness with the current multidisciplinary orthopaedic rehabilitation.

**Research questions.** The primary research question refers to the effectiveness of the interprofessional rehabilitation program compared to the multidisciplinary orthopaedic rehabilitation. The focus is directed on factors that relate to active self-management, e.g. self-reported functional ability, pain related cognitions, physical activity. *Primary hypothesis:* Adults with chronic non-specific low back pain who participate in an interprofessional rehabilitation program will show significantly improved functional ability 12 months after completion of the program in comparison to adults with chronic non-specific low back pain who participate in the standard multidisciplinary orthopaedic rehabilitation. Secondary hypotheses refer to mechanisms of action of the interprofessional rehabilitation program and its effectiveness regarding important risk factors for the development of chronic non-specific low back pain (Yellow Flags).

**Study design/ methods.** A multicentre prospective quasi-experimental control group design with three time points of measurement will be performed. Temporal sampling with consecutive inclusion of adults with chronic non-specific low back pain are first assigned to a control condition (usual care; n = 294), and after subsequent implementation of the interprofessional rehabilitation program, to an intervention condition (interprofessional rehabilitation, n = 294). To evaluate the effectiveness data of participant are recorded at baseline, discharge, and 12 months.

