**Outcomes.** Primary outcome is the level of functional ability 12 months after the end of inpatient rehabilitation measured by the Hannover Functional Ability Questionnaire (FFbH-R). Secondary outcome measures include pain-related cognitions, emotions and behaviour, pain intensity, physical activity, health-related quality of life, time off work and medical visits due to low back pain during the last six month.

**Sample.** N=588; Participants with chronic non-specific low back pain with the following assignment diagnoses M54.4 – M54.9 as well as M51.2 – M51.9 and M53.8 – M53.9 according to ICD-10.

**Sample Size and Power Calculation.** Sample power (Software: G-Power 3.0) concerning the primary outcome is approximated for an analysis of covariance at t3 with a small effect size of Cohen's  $d=0.3$ , a 2-sided  $\alpha=0.05$  and a test power of  $1-\beta=0.8$ . This approximation results in a sample size of at least 352 participants with complete data for both study groups ( $n=176$  per group). Anticipating a dropout rate of 40%, it is necessary to include 588 participants ( $n=294$  per group).

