### III. Disclosures on the study participants

1. Number (*in case of comparing studies please indicate the division in groups*)

- 588 participants in total
- 294 study participants each in the intervention and control group

In case of Zero-hypothesis-studies:

Was there a formal estimation of sample size?

☒ Yes      ☐ No

2. Age and sex (please indicate the age of the participant and the maximum and minimum limit seen as exclusion criteria)

We aim at a ratio of male to female participants which is representative to the German inpatient rehabilitation of chronic non-specific low back pain. The defined age range includes participants between 18 and 65 years. Age-specific and gender-specific effects of the intervention will be tested.

3. Are the participants:

- ☐ Healthy people
- ☐ Pregnant or breastfeeding women
- ☐ Children and teenagers
- ☒ Relevant diseased (please indicate disease and it's stage)
- ☐ Persons who suffer from other diseases? (Especially: psychological diseases which evoke doubts of the legal competence or the capacity to understand the wrongfulness of an act)

Participants with chronic non-specific low back pain with the following assignment diagnoses (ICD-10, German version): M51.2-M51.9, M53.8, M53.9 and M54.4-M54.9. The stage of chronicity is determined during the study; moderator analyses will be performed with regard to the effectiveness of the intervention.

4. Which further criteria of inclusion are intended (e.g. permitted additional medicine)?

There are no further criteria of inclusion.

5. Which further criteria of exclusion are intended (e.g. advanced kidney or liver insufficiency, forbidden additional medicine etc.)?

- specific underlying diagnosis of back pain (e. g. radicular symptoms, myelopathy, formerly performed spine surgeries, inflammatory deformations of the spine)
- considerably reduced health status (e.g. comorbidities such as severe heart disease)
- age below 18 years or over 65 years
- inability to speak German
- considerably reduced sight and hearing (not corrected)
- severe psychiatric condition as secondary diagnosis
- current application for early retirement or invalidity pension (§§ 51 SGB V)

6. Are people who have legally or officially been sent to a mental institution supposed to take part in the study?

☐ Yes      ☒ No

7. Are people who have already taken part in other studies supposed to take part in this study?

☐ Yes      ☒ No

How long ago does the last participation have to be?

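### In a non-randomised sequential-cohort comparison, the protocol ties covariate adjustment to baseline differences and does not ensure that known prognostic factors enter the primary model

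*Protocol*

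**What the plan says.** The abstract (section II, item 2) describes the design: "A multicentre prospective quasi-experimental control group design with three time points of measurement will be performed". Allocation is by period: "Temporal sampling with consecutive inclusion of adults with chronic non-specific low back pain are first assigned to a control condition", with the intervention cohort enrolled after the new programme has been implemented. In section II, item 8 the box for randomisation is left unticked.

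The statistical methods are in section II, item 12 b). For the primary outcome, "t-test or analysis of covariance (ANCOVA) respectively of functional ability measured with the FFbH-R at the 12-month follow-up will be used", and the same sentence continues "adjusted for baseline differences, as primary analysis". No covariate is named there, not even baseline FFbH-R. The next sentence turns to other variables: "Further possible baseline differences between both study groups in secondary variables (e.g. socio-demographic, medical) will be also addresses via regression analyses", or by analysis of covariance. It gives examples and no list, does not say what counts as a difference, and does not say whether these variables belong to the primary model.

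The sample-size paragraph of the abstract mentions only one of the two methods: it "is approximated for an analysis of covariance at t3 with a small effect size of Cohen's" d = 0.3.

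Candidate covariates appear elsewhere. The secondary outcomes include "pain intensity, physical activity, health-related quality of life, time off work and medical visits due to low back pain", and the abstract has data recorded at baseline, discharge and 12 months. Section III, item 2 plans tests of age- and gender-specific effects. Item 3 adds: "The stage of chronicity is determined during the study; moderator analyses will be performed". These last two concern effect modification, not control of confounding.

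**The concern.** In a randomised trial, baseline imbalance is chance and covariate adjustment mainly buys precision. Here the cohorts differ by calendar period, and with it possibly by referral pattern, centre mix and willingness to take part, so imbalance can be systematic. The confounding a variable causes is its imbalance multiplied by its association with the outcome. A plan that looks only at the imbalance can pass over a strong prognostic factor whose difference looks unremarkable.

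Three features of item 12 b) leave this open: adjustment is linked to differences; a t-test, which by itself carries no covariates, is a permitted primary analysis; and the socio-demographic and medical variables stand in a sentence after the one that defines the primary analysis. At stake is whether the 12-month FFbH-R contrast keeps confounding that the trial's own baseline data could remove.

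**Working it through.** **1. The plan's own figure.** Inputs from the abstract: d = 0.3, two-sided alpha 0.05, power 0.80, dropout 40%.
- Normal approximation: n = 2(1.96 + 0.842)²/0.3² = 174.4, so 175 per group. The t-test version gives 175.4, so 176.
- Dropout: 176/(1 - 0.4) = 293.3, so 294 per group and 588 in total.

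The sample size reproduces.

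**2. How often an imbalance would show.** For a true standardised imbalance δ with n per group, P(p<0.05) = Φ(δ/√(2/n) - 1.96) + 1 - Φ(δ/√(2/n) + 1.96). Example with δ = 0.15 and n = 176: √(2/176) = 0.1066; 0.15/0.1066 = 1.407; Φ(-0.553) + 1 - Φ(3.367) = 0.291.

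| True imbalance | 176 per group | 294 per group |
|---|---|---|
| 0.10 SD | 0.155 | 0.228 |
| 0.15 SD | 0.291 | 0.444 |
| 0.20 SD | 0.467 | 0.679 |

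**3. Bias from one omitted covariate.** Bias = imbalance × coefficient (SD of outcome per SD of covariate, given baseline FFbH-R). The protocol gives neither, so both are assumed: imbalance 0.10-0.20 SD, coefficient 0.2-0.4. The range is 0.10 × 0.2 = 0.02 SD to 0.20 × 0.4 = 0.08 SD, or 7% to 27% of d = 0.3.

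**4. Average effect of a difference-triggered rule.** Simulation with 4,000 runs per scenario, 176 per group and no true treatment effect. Baseline outcome is always adjusted for (coefficient 0.6). The confounders are mutually independent and all act in the same direction. Three models are compared: no further covariates; covariates kept only if p<0.05 at baseline (an assumed rule); all confounders fixed in advance. Entries are mean bias in SD / type I error.

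| Confounders, imbalance, coefficient | None | Selected | Fixed |
|---|---|---|---|
| 1, 0.15, 0.3 | 0.045 / 9.1% | 0.020 / 5.6% | 0.000 / 5.2% |
| 3, 0.15, 0.2 | 0.090 / 18.4% | 0.043 / 7.4% | 0.000 / 5.1% |
| 3, 0.20, 0.2 | 0.120 / 28.6% | 0.038 / 7.7% | -0.001 / 5.7% |
| 5, 0.10, 0.2 | 0.101 / 21.2% | 0.061 / 9.2% | 0.001 / 4.6% |
| 5, 0.15, 0.2 | 0.149 / 40.2% | 0.070 / 12.3% | -0.001 / 5.2% |
| 5, 0 (no confounding), 0.2 | -0.001 / 5.4% | -0.001 / 4.8% | -0.001 / 5.9% |

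The Monte Carlo standard error of a 5% rejection rate is √(0.05 × 0.95/4000) = 0.34 percentage points. In the confounded scenarios, selection leaves 0.020/0.3 = 7% to 0.070/0.3 = 23% of the planned effect. In the last row, selection does not inflate the error rate.

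**5. Worst case.** The largest non-significant observed difference at 176 per group is 1.967 × 0.1066 = 0.21 SD. Three covariates all at that limit, in the same direction, with coefficients of 0.2-0.3, leave 3 × 0.21 × 0.2 = 0.13 to 3 × 0.21 × 0.3 = 0.19 SD. Without rounding the limit (0.2097), that is 42-63% of d = 0.3. At 294 per group the limit is 0.162 SD and the total 0.10-0.15 SD (32-49%).

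**The case against.** The best defence is that the protocol commits to adjustment, names the variable domains and the tools, and may leave the covariate list to a statistical analysis plan. The word *possible* could mean every potential difference, all adjusted. The primary-analysis sentence is not limited to FFbH-R, so the further variables may be meant for the same model. This has force: a missing list alone would be no finding. What stands against it is the stated principle. Linking adjustment to differences and allowing a t-test suit a non-randomised contrast badly, and an analysis plan that follows the protocol would inherit both.

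A reader might also infer stronger things that the document does not support:
- *Covariates will be chosen by significance testing.* No test, p-value or threshold is stated. The p<0.05 rule above is an assumption used to put a size on the problem.
- *Confounding is known to stay in the primary estimate.* The text leaves it uncontrolled; it does not show that it is present.
- *About half the planned effect is at risk.* The 42-63% needs every imbalance at the limit, in one direction and unselected, with non-overlapping effects. Chronicity, pain intensity and time off work plausibly overlap.
- *Data-driven selection itself breaks the error rate.* Without systematic imbalance the simulated rate was 4.8%. The inflation comes from the imbalance.
- *The cited methods paper is misapplied because its title concerns randomised trials.* A title cannot settle that, and ANCOVA is not confined to randomised trials.

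**Conclusion.** The point holds in a limited form. For a comparison of consecutive cohorts, item 12 b) does not ensure that known prognostic factors enter the primary model, and nothing elsewhere in the protocol repairs this. The plausible size is moderate: an average residual bias of 0.02-0.07 SD and type I error of about 6-12%, with 0.13-0.19 SD as a worst case only. These figures rest on assumed imbalances, coefficients, number and direction of confounders, and on an assumed selection rule. The document supplies none of them, and a single weak confounder would leave little bias. The change is worth making because it is cheap and bears on the primary contrast. It would not make the cohorts comparable in every respect: calendar period coincides with group, and no covariate adjustment can separate the two.

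**What to change.** In section II, item 12 b), delete the t-test option and define the primary analysis as an ANCOVA of 12-month FFbH-R with a covariate set fixed in advance and included regardless of observed group differences: baseline FFbH-R, age, sex, baseline pain intensity, baseline time off work, centre, and stage of chronicity if it is measured at baseline. Section III, item 3 does not give the time of that measurement, so the sponsor should state it. Replace the sentence on further differences accordingly, so that no covariate's entry depends on the size of its observed imbalance. A propensity-weighted estimate may be added as a sensitivity analysis.

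The cost is a rewritten passage, a few degrees of freedom out of roughly 350 (the exact number depends on the number of centres, which is not stated) and a rule for missing covariate values. The planned 588 participants need not change. The report should say plainly that calendar-period effects remain.

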### III. Disclosures on the study participants

1. Number (*in case of comparing studies please indicate the division in groups*)

- 588 participants in total
- 294 study participants each in the intervention and control group

In case of Zero-hypothesis-studies:

Was there a formal estimation of sample size?

☒ Yes      ☐ No

2. Age and sex (please indicate the age of the participant and the maximum and minimum limit seen as exclusion criteria)

We aim at a ratio of male to female participants which is representative to the German inpatient rehabilitation of chronic non-specific low back pain. The defined age range includes participants between 18 and 65 years. Age-specific and gender-specific effects of the intervention will be tested.

3. Are the participants:

- ☐ Healthy people
- ☐ Pregnant or breastfeeding women
- ☐ Children and teenagers
- ☒ Relevant diseased (please indicate disease and it's stage)
- ☐ Persons who suffer from other diseases? (Especially: psychological diseases which evoke doubts of the legal competence or the capacity to understand the wrongfulness of an act)

Participants with chronic non-specific low back pain with the following assignment diagnoses (ICD-10, German version): M51.2-M51.9, M53.8, M53.9 and M54.4-M54.9. The stage of chronicity is determined during the study; moderator analyses will be performed with regard to the effectiveness of the intervention.

4. Which further criteria of inclusion are intended (e.g. permitted additional medicine)?

There are no further criteria of inclusion.

5. Which further criteria of exclusion are intended (e.g. advanced kidney or liver insufficiency, forbidden additional medicine etc.)?

- specific underlying diagnosis of back pain (e. g. radicular symptoms, myelopathy, formerly performed spine surgeries, inflammatory deformations of the spine)
- considerably reduced health status (e.g. comorbidities such as severe heart disease)
- age below 18 years or over 65 years
- inability to speak German
- considerably reduced sight and hearing (not corrected)
- severe psychiatric condition as secondary diagnosis
- current application for early retirement or invalidity pension (§§ 51 SGB V)

6. Are people who have legally or officially been sent to a mental institution supposed to take part in the study?

☐ Yes      ☒ No

7. Are people who have already taken part in other studies supposed to take part in this study?

☐ Yes      ☒ No

How long ago does the last participation have to be?

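### The stated primary model has no centre term, although the groups are formed by calendar phase, so a shift in centre mix between phases can enter the treatment estimate

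*Protocol*

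**What the plan says.** Protocol, II.2 (study design): "A multicentre prospective quasi-experimental control group design with three time points of measurement will be performed". On how patients reach a group: "Temporal sampling with consecutive inclusion of adults with chronic non-specific low back pain are first assigned to a control condition". The intervention phase follows once the programme has been put in place. Section II.8 ticks open and multicentric and leaves randomised unticked.

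Protocol, III.1 gives the division into groups as "294 study participants each in the intervention and control group". The abstract gives the same totals. The text sets no number per centre or per centre and phase.

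Protocol, II.12 b) names a t-test or ANCOVA of the FFbH-R at 12 months, which "will be used, adjusted for baseline differences, as primary analysis". A separate sentence allows further adjustment for secondary variables, with socio-demographic and medical variables as examples. Centre is not mentioned as a factor, covariate or stratum, either there or in the sample size paragraph.

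**The concern.** In a trial randomised within centres, both groups have the same centre mix in expectation, and leaving centre out of the model costs only some precision. Here calendar phase decides the group, so nothing in the allocation holds the mix constant. A centre that recruits or retains relatively more patients in one phase than in the other carries its case mix and its team's results into one group. A model that pools the centres cannot separate this from the effect of the programme.

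The protocol gives two reasons why the mix might move. Control care is delivered mainly in open groups, whereas the programme needs fixed groups of eight to twelve, so centres may not keep the same relative pace. The protocol also plans for 40% dropout and has the centres run the questionnaire survey, so retention may vary by centre and phase. Neither shows that the mix will shift.

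The planned effect is small, so even a moderate bias is a noticeable fraction of it.

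**Working it through.** **1. The plan's own figure.** Inputs from the abstract's sample size paragraph: d = 0.3, two-sided alpha 0.05, power 0.80, dropout 40%.

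- The noncentral t distribution gives power 0.7991 at 175 per group and 0.8014 at 176, so 176 per group.
- A one-covariate ANCOVA with f = 0.15 needs 351 in total, so 352 with equal groups. This agrees with "This approximation results in a sample size of at least 352 participants with complete data for both study groups".
- Dropout: 176 / (1 − 0.4) = 293.3, rounded up to 294 per group and 588 in total, as in "Anticipating a dropout rate of 40%, it is necessary to include 588 participants".

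The stated size reproduces. The point concerns bias, not a wrong number.

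**2. Bias without a centre term.** Take two kinds of centre. Let g be the gap in 12-month FFbH-R between them, in SD, that remains after baseline adjustment. Let s be the change between phases in the share of one kind among those analysed. Then

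bias = s × g.

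Neither quantity is in the documents. The ranges used here, s from 10 to 40 percentage points and g from 0.1 to 0.5 SD, are assumptions.

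The standard error at 176 per group with SD = 1 is √(2/176) = 0.1066. With δ = bias / 0.1066, the probability of rejection when the programme has no effect is Φ(−1.96 + δ) + Φ(−1.96 − δ).

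| Shift s (assumed) | Gap g (assumed) | Bias, SD | Share of 0.3 | δ | Type I error |
|---|---|---|---|---|---|
| 10 points | 0.1 | 0.01 | 3% | 0.09 | 0.051 |
| 20 points | 0.3 | 0.06 | 20% | 0.56 | 0.087 |
| 30 points | 0.3 | 0.09 | 30% | 0.84 | 0.135 |
| 40 points | 0.5 | 0.20 | 67% | 1.88 | 0.467 |

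The sign depends on which centres gain share. If a bias of 0.06 SD runs against the programme, a true effect of 0.30 appears as 0.24, and power falls to Φ(0.24/0.1066 − 1.96) = Φ(0.29) = 0.61. If s = 0 or g = 0, the bias is zero.

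**3. Price of a centre term.** With two kinds of centre whose shares are 0.5 + s/2 in one phase and 0.5 − s/2 in the other, the within-centre information is (n/2)(1 − s²), compared with n/2 when the mix is equal. Power is Φ(0.3 × √(88(1 − s²)) − 1.96). The evaluable number needed is 176 / (1 − s²), and enrolment is that number divided by 0.6.

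| Shift s | 1 − s² | Power at 176 per group | Evaluable per group needed | Enrolled per group needed |
|---|---|---|---|---|
| 0 | 1.00 | 0.80 | 176 | 294 |
| 10 points | 0.99 | 0.80 | 178 | 297 |
| 20 points | 0.96 | 0.79 | 184 | 307 |
| 30 points | 0.91 | 0.77 | 194 | 324 |
| 40 points | 0.84 | 0.73 | 210 | 350 |

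Steps 2 and 3 take the residual SD as 1 and give no credit for the precision gained from the baseline covariate.

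**The case against.** The strongest objection is scope. Section II.12 b) is a short answer on an ethics committee form. Whether centre enters an ANCOVA is often settled in a statistical analysis plan, and one may exist that adds it. The wording does not exclude centre, and the list of further variables is only illustrative. This limits the point but does not remove it. The protocol itself states its primary model and the adjustment in it. The illustrative list belongs to a separate sentence on secondary variables, and centre is neither socio-demographic nor medical. In a design without randomisation, the choice bears on validity and not only on precision.

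The second objection is that baseline adjustment already deals with centre differences. It does so in part: differences visible in baseline FFbH-R are removed, which is why g above is defined after that adjustment. Differences in team or care that act after baseline stay. A plain t-test of the 12-month score, which the protocol also allows, removes neither.

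Three stronger readings are tempting and should be resisted.

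- A reader might infer that the comparison is biased. The documents do not say that the mix will differ or that centres differ in outcome, and both are needed.
- A reader might infer that the protocol must fix equal numbers per centre and phase. That is an operational choice, and quotas at enrolment would not secure balance among completers with 40% dropout. The total of 294 per group is not itself an error.
- A reader might infer that leaving centre out harms the trial even with equal mixes. In that case only some precision is lost and the test is slightly conservative.

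**Conclusion.** The point holds as a weakness of the stated primary model: groups are formed by phase, several centres contribute, and no centre term protects the comparison against a change in centre mix. It is a risk and not a demonstrated bias. Its size cannot be derived from the documents, because the text gives neither the number of centres nor their differences. The results of 0.01 to 0.20 SD, with type I error from about 0.05 to about 0.47, rest wholly on the assumed shifts and gaps. The low end is negligible and the high end would be two thirds of the planned effect. The sample size calculation is correct as stated.

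**What to change.** In II.12 b), define the primary analysis as an ANCOVA of 12-month FFbH-R on group, with baseline FFbH-R as covariate and centre as a fixed effect. Drop the plain t-test as an alternative. Commit to a table of participants enrolled and analysed by centre and phase, so that any shift in mix can be seen. Similar control and intervention numbers within each centre are desirable, because they preserve power, but they are not a condition for the analysis.

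The cost is a few degrees of freedom. If the mix stays similar, 294 per group remains adequate. If it shifts, power at 176 evaluable per group falls to about 0.79 at 20 points and 0.73 at 40 points, so it would be wrong to promise that the change never needs more patients. The centre term does not remove differences between the phases that are due to calendar time, and the protocol should not claim that it does.
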